## Methods

### Study design

A single institution 1:1 randomized controlled open-label trial with two parallel arms, powered for superiority, has been designed in accordance with the CONSORT statement and Helsinki declaration. The study has been approved by the local Ethical committee [n. 2013/0009390] and funded by the Italian Ministry of Health [GR-2011-02351711].

### Participants and setting

All patients with highly suspicious or diagnosed primary NSCLC are screened for eligibility criteria within the Lung Cancer Multi-Disciplinary Team Meeting at Arcispedale Santa Maria Nuova (ASMN) of Reggio Emilia, Italy. This is an Institute for Advanced Technologies and Healthcare Protocols in Oncological Research certified by the Organization of European Cancer Institutes in 2014. The Thoracic Surgery Unit’s catchment area covers a range of about 535,000 inhabitants and performs an average of 500 operations per year, including about 130 lung resections for malignancies.

Patients with Stages I and II NSCLC are considered for enrolment if they qualify for surgery. We exclude candidates who require adjuvant therapies and patients unfit for the physical exercise required by intervention [Table 1]. In patients affected by COPD, medical treatment is reviewed and optimized according to the most recent Global Initiative for Chronic Obstructive Lung Disease guidelines at the start of the selection process, to minimize confounding factors.

**Table 1 Tab1:** Inclusion and exclusion criteria

Inclusion criteria	Exclusion criteria
Patients affected by NSCLC in Stage I-II	Tumour stage requiring adjuvant therapies
Patients eligible for lung resection	Patients unfit for the type of physical exercise included in study protocol
Patients able to walk autonomously without medical devices (e.g., crutches)	Patients affected by sensorial or cognitive deficits with potential severe impact on compliance (deafness, blindness, dementia, etc.)
Patients able to give informed consent	

Written informed consent is obtained from participants by the operating surgeon during the preoperative consultation. Subsequently, patients undergo baseline assessment and afterwards are randomized to receive intensive PR (Intervention Group - IG) or SC (Control Group - CG) (Fig. 1).

**Fig. 1 Fig1:**
[figure not shown]
Study Flow diagram. Legend: MDT = Multi-Disciplinary Team; PR = pulmonary rehabilitation; Preop = preoperative; Postop = postoperative

### Measurements

Patients included in the study are assessed at baseline (T0), the day before surgery (T1), one month after surgery (T2) and six months after surgery (T3) [Table 2].

**Table 2 Tab2:** Assessments

	T0 Baseline	Randomization	T1 1 day before surgery (14÷21 days from baseline)		T2 (1 month ± 5 days after surgery)		T3 (6 months ± 5 days after surgery)	
			IG	CG	IG	CG	IG	CG
Pulmonary function (PFTs)	x		x				x	x
Exercise capacity (6MWT)	x				x	x	x	x
Quality of life (SF-12)	x						x	x
Mood disturbances (HADS)	x	Randomization	x	x			x	x
Pain (NRS)	x				x	x	x	x
Length of stay					x	x		
Postoperative complications					x	x	x	x

*IG* Intervention Group, *CG* Control Group, *PFTs* Pulmonary Function Tests, *6MWT* Six-Minute Walk Test, *SF-12* Short form 12, *HADS* Hospital Anxiety and Depression Scale, *NRS* Numeric Rating Scale

Baseline assessments are carried out immediately before randomization (T0) and include lung function, exercise capacity, QoL, mood disturbances and pain.

Static and dynamic respiratory volumes and DLCO are measured with full pulmonary function tests (PFTs). Exercise capacity is evaluated with 6MWT, according to current guidelines [11, 26]. Data on QoL are assessed with SF-12 [27], mood disturbances are evaluated using the HADS [28] and pain is quantified using the NRS [29].

The day before surgery (T1), all patients are re-assessed for mood disturbances. PFTs are repeated in the IG; treatment-related side effects and patient adherence to the intensive preoperative PR are also recorded.

One month after surgery (T2), patients repeat exercise capacity and pain evaluation using the same tools employed at baseline (T0). Data regarding LoS, postoperative complications and 30-day mortality are also recorded at this stage. Postoperative complication categories include acute respiratory failure, cardiac failure (including myocardial infarction), surgical site infection (including pneumonia and bronco-pleural fistula), arrhythmias (including atrial fibrillation), thrombosis and pulmonary embolism, neurological impairment (including stroke) and other (specified).

Long-term follow-up takes place 6 months after surgery (T3) and includes the assessment of lung function, exercise capacity, QoL, mood disturbances, pain and late postoperative complications. In the IG, patient adherence to the intensive postoperative PR and side effects are also recorded at 6 months.

To tailor the intensity of training, at T0 and T2 (immediately before initiation of pre- and postoperative PR) patients in IG perform:

- Shuttle walking test, to determine initial intensity of aerobic training [30];

- 10 repetition maximum test, to determine initial load of resistance training [31].

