### Additional assessments

Data regarding patient compliance and treatment-related side effects during both preoperative and postoperative intensive PR will also be collected.

Intensive PR includes the implementation of hospital-based and home-based training. Patients randomized to the treatment group are requested to register the activities performed at home on a training log; distance in kilometres, number of steps and heart rate achieved during aerobic walking and exercises performed during respiratory muscle training (RMT) session are recorded. As patient adherence to protocol is a crucial issue in rehabilitation and the literature recommends the consistent and explicit reporting of exercise attendance in people with respiratory diseases [24], the proportion of training sessions performed are collected to assess patient compliance: adherence to the protocol is defined as the achievement of 80% or more of the training exercises prescribed [25].

We consider as minor side effects self-reported pain or discomfort in the muscles/joints involved with the physical component of the treatment; major side effects include any trauma secondary to a fall requiring specific interventions or symptomatic alterations of the basic vital signs (i.e., blood pressure, heart rate) arising during or shortly after the end of exercise and confirmed by instrumental measurement.

To evaluate the actual effect of lung resection on the study population before the postoperative treatment, FEV1, FVC and DLCO are also registered in the experimental group one month after surgery and compared to baseline.

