##### 2.4.2.1.Preoperative intensive PR

Preoperative intensive PR is organised into six outpatient sessions performed two to three times per week, plus eight home-based sessions performed three to four times per week. The overall duration of this treatment ranges from 14 to 21 days, starting the same day the patient is listed for surgery or immediately afterwards, to minimize the delay in offering surgical treatment and to avoid the 30-day breach, as recommended by the regional guidelines [32].

Each outpatient session lasts approximately two hours and consists of an individual, supervised and personalised combination of the following elements:Therapeutic education, whose contents are the same as those provided to CG. It is delivered during the first outpatient session and repeated, if necessary, during the course of the treatment.Aerobic training, which consists of 30 to 40 min on a cycle ergometer. This training is maintained at the intensity of 60–80% peak workload (previously determined with shuttle walking test) [30] and includes a 5-min warm up and a 5-min cool down. Within this range, the intensity of training is adapted to the patient’s tolerance.Resistance training for lower limbs (extensor muscle group), upper limbs (biceps, triceps, deltoids, latissimus dorsi, pectoralis) and abdominal wall. Each exercise is performed for two to three sessions of 10 repetitions at the maximal load (previously determined with the 10-repetition maximum test) [31];RMT which includes breathing pattern training, PEP training and inspiratory muscle training for at least 15 to 30 min. Inspiratory muscle training is performed by means of a pressure threshold device, with a load ≥30% of maximal predicted inspiratory pressure; intensity is adapted to the patient’s tolerance.

Each home-based session lasts approximately one hour and consists of an individual, unsupervised and personalised combination of RMT, performed twice a day, plus 30 min of aerobic walking at the intensity of 60–80% of maximal heart rate. Patients are given a portable pedometer and a heart rate monitor and are requested to record their adherence to home-based training in the training log, which collects kilometres, steps and heart rate achieved during aerobic walking and exercises performed during RMT session.

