##### 2.4.2.2.Postoperative intensive PR

Postoperative PR starts one month after surgery and includes 39 sessions divided into 15 outpatient sessions performed twice a week and 24 home-based sessions performed three times per week. Overall, the postoperative PR programme lasts 8 weeks.Each outpatient session takes approximately two hours and 15 min and includes both aerobic and resistance training, following the same procedures described for preoperative PR, plus RMT for the first eight sessions. In addition, outpatient postoperative PR includes 10 min of scar massage during the first four weeks and group bodyweight exercise training, scheduled once a week for the entire duration of the programme.Each home-based session lasts approximately one hour and consists of an individual, unsupervised and personalised combination of RMT performed twice a day and 30 min of aerobic walking at the intensity of 60–80% of maximal heart rate, monitored by patients with the portable device provided. Once again, patients are requested to record their adherence to home-based training by the training log.

At the end of postoperative PR, patients are advised to continue aerobic training and RMT until the 6-month follow-up is completed (T3).

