The definition of the best PR treatment programme required a careful review of the current literature [23], resulting in the definition of the following key elements:The inclusion of both aerobic and strength training of lower and upper limb muscles [2, 11, 35];The combination of outpatient and home-based treatment sessions. This should facilitate the enrolment of patients referred from provincial hospitals and might increase their compliance, minimizing the risk of attrition bias;The inclusion of inspiratory muscle training, incentive spirometry, airway clearance techniques and/or respiratory exercises, as lung cancer leads to respiratory impairment and COPD is a frequent comorbidity in patients affected by lung cancer [19, 20, 36, 37];The inclusion of group exercise training sessions during the postoperative phase, alongside individual guided and monitored home-based training, to facilitate mutual support among patients with NSCLC, whose vulnerable psychosocial condition could affect postoperative functioning and QoL [38]. In fact, a recent systematic review examining the spectrum of health care needs among people with lung cancer showed that psychological, emotional and social needs were most frequently specified and lack of acknowledgement of patients’ status by others were perceived as important issues [39]. Therefore, group sessions may facilitate the sharing of feelings, experiences and concerns, and may support patients in coping with their illness;The inclusion of scar massage in the postoperative phase to relieve tissue tension and reduce pain. In our clinical experience, patients frequently report pain and hypersensitivity around surgical scar.

At the time of planning this protocol, we estimated an overall 10% withdrawal rate, mainly due to perioperative morbidity and mortality, as well as unforeseen N1/N2 lymph nodal involvement diagnosed after surgery and requiring adjuvant therapies. However, more recent literature suggests a greater incidence of intraoperative lymph nodal upstaging [40] and even when an accurate staging workup is performed, including PET/CT and EBUS-TBNA when appropriate, minimal involvement of hilar nodes (N1 stage) remains difficult to assess preoperatively. Furthermore, more aggressive protocols are recommended by international guidelines in treating N1 NSCLC [41]. A greater than expected number of patients may therefore withdraw post randomization to ensure they receive the best cancer care.

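### Side effects are recorded only in the intervention arm under a minor-event definition with no onset or attribution rule, so the postoperative count may misstate the harm due to the programme

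*Protocol article*

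**What the plan says.** The protocol article treats side effects under Additional assessments, next to compliance: "treatment-related side effects during both preoperative and postoperative intensive PR will also be collected". Only the intervention group (IG) receives intensive PR.

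The Measurements section fixes who is asked and when. For the day before surgery (T1): "PFTs are repeated in the IG; treatment-related side effects and patient adherence to the intensive preoperative PR are also recorded". The other two items in that sentence belong to the IG, so by context the side effects do too. For six months (T3) the arm is explicit: "In the IG, patient adherence to the intensive postoperative PR and side effects are also recorded at 6 months". Table 2 has no row for side effects, and the Statistical analysis section lists no comparison of them.

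The minor category reads: "We consider as minor side effects self-reported pain or discomfort in the muscles/joints involved with the physical component of the treatment". The major category has two parts: trauma from a fall that needs specific intervention, and symptomatic vital-sign changes. The vital-sign changes must be events "arising during or shortly after the end of exercise and confirmed by instrumental measurement".

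**The concern.** The trial is randomised, but the side-effect item is collected in one arm. Its minor category is defined by where the patient hurts, and does not ask when the pain began or why. Patients who have had a chest operation may hurt in the same region whether or not they exercised. A percentage from the IG alone cannot separate programme effects from what the control group (CG) would also have reported.

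The Conclusion section hopes to support systematic use of perioperative rehabilitation. For that purpose a reader needs to know whether the programme adds musculoskeletal pain or falls over standard care. A later analysis plan cannot supply this, because control answers that were never collected cannot be recovered.

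**Working it through.** **Step 1. Does the definition overlap with surgical pain?** The resistance work trains lower limbs, then "upper limbs (biceps, triceps, deltoids, latissimus dorsi, pectoralis) and abdominal wall" (Preoperative intensive PR). From one month after surgery, each outpatient session "includes both aerobic and resistance training, following the same procedures described for preoperative PR" (Postoperative intensive PR). The Discussion states that "patients frequently report pain and hypersensitivity around surgical scar". That shoulder, chest and abdominal-wall muscles overlap with the region that hurts after chest surgery is an inference from the muscle list; the article itself names only the scar area. The overlap exists only after surgery. Events recorded at T1 precede the operation.

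**Step 2. Which parts of the definition lack a link to exercise?** Minor pain has no onset, change-from-baseline or attribution criterion. Fall trauma, as worded, need not occur in a session, and controls are also advised to stay active after discharge. Vital-sign events are tied to exercise, so the problem does not reach them.

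**Step 3. Do other two-arm data supply the background?**

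- NRS pain is taken in both arms at T0, T2 and T3 and compared by t-test. As described it carries no body site, and it is not scheduled at T1.
- Postoperative complications are recorded in both arms at T2 and T3 and compared by chi-square test. The named categories contain neither musculoskeletal pain nor falls; a residual category for other events is not systematic questioning.

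**Step 4. What size could the error have?** The article gives no side-effect rate, so nothing of the plan's can be reproduced on this item. The sample size supplies the number of evaluable patients. With d = 0.5, two-sided alpha 5% and power 80%, n = 2(1.96 + 0.8416)² / 0.5² = 62.8, so 63 per arm; 63 / 0.9 = 70 per arm, 140 in total, which matches the plan.

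Let b be the background rate and e an independent programme effect, both assumed. The IG rate is p = b + e − be and the true difference is p − b. If p is read as programme harm, the excess is p − (p − b) = b. If both arms were asked, the 95% half-width would be 1.96 × √[p(1−p)/63 + b(1−b)/63].

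| b | e | IG rate p | True difference | Excess if p is read as harm | Half-width with both arms asked |
|---|---|---|---|---|---|
| 0% | 10% | 10% | 10 points | 0 | ±7.4 points |
| 20% | 10% | 28% | 8 points | 20 points | ±14.8 points |
| 40% | 10% | 46% | 6 points | 40 points | ±17.3 points |
| 50% | 10% | 55% | 5 points | 50 points | ±17.4 points |

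Over an assumed background of 0% to 50%, the excess runs from 0 to 50 points.

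**Step 5. Could the error go the other way?** Postoperative PR starts at one month and lasts 8 weeks, so it ends about three months after surgery. The only stated postoperative recording point is six months, some three months later. If a share r of events is captured, the recorded rate is r × p, which falls below the true difference when r < (p − b)/p. At b = 20% and e = 10% that threshold is 0.08 / 0.28 = 0.29. At b = 0% any loss understates. The direction of the net error is therefore not fixed by the document.

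**The case against.** The strongest reply is that this is a tolerability record and was never meant as a harm estimate. Side effects appear in neither the secondary aims nor the secondary outcomes, no test of them is planned, and they are labelled treatment-related. Pain and complications, the harms that both arms can share, are compared between arms. A journal article may also leave onset and attribution rules to a full protocol or case report form that is not shown.

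Much of this stands, and it limits the point. A reader might infer that the programme's harm will be overstated, or that the trial has no controlled harm data at all. The documents support neither reading. They give no background rate and plan no attributable-harm figure, and late recall could lower the count (step 5). Two-arm comparisons of pain score and complications do exist. Nor does surgical pain touch the preoperative count.

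What does not stand is that the label settles attribution. The article calls the events treatment-related and then defines the minor ones by site alone, in an open-label trial, while giving an exercise link to vital-sign events in the same sentence. The choice of arm is also stated in the article and is not a detail left to another document.

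**Conclusion.** The point holds in limited form. For postoperative minor muscle or joint pain, and for falls with injury, the plan yields an IG count with no like-for-like control count. That count may misstate the harm attributable to the programme, in a direction and by an amount that the documents do not allow one to estimate. The table in the working is illustration only: it rests on assumed rates, an independent programme effect and 63 evaluable patients per arm.

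Preoperative events are not affected by surgical pain, though they too have no control count. The vital-sign criterion is sound on this point, and the primary analysis of 6MWD change is unaffected. This is a cheap improvement worth making; it does not threaten the main result.

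**What to change.** - Ask both arms the same short items at T1, T2 and T3: muscle or joint pain or discomfort by body region, and fall with injury. Controls already attend all three visits. T2 comes immediately before postoperative PR starts, so it also gives a postoperative reading before that training begins.
- Report the between-arm difference with its 95% CI. At about ±15 to ±17 points under background rates of 20% to 40% and a 10% programme effect it would be imprecise, but it would be a randomised comparison.
- If the change comes mid-trial, restrict that comparison to patients enrolled after it, so that early IG patients are not set against late controls.
- Keep IG events that arise during or shortly after sessions, including vital-sign events, as a separate descriptive line.
- Describe any IG-only count as tolerability and not as attributable harm.

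The cost is a short CRF page and one amendment, with no new visit or staff. The downside is that patients already past a visit will have no control data. Enrolment began in 2015 and results were expected by the end of 2017, so a late change would cover few patients. In that case the last two steps can still be taken in full.

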### Treatment protocols

Patients randomized to CG are provided with the SC already in place in our hospital. Patients randomized to IG follow an evidence-based intensive PR programme developed by the research group and delivered in addition to SC.

#### Control group

Patients allocated to CG receive SC, which consists of one therapeutic education session delivered by physician and physiotherapist the day before surgery and early inpatient postoperative PR, delivered by physiotherapist. The therapeutic educational session lasts 30 to 40 min and involves counselling and self-care management. The aim of counselling is to prepare the patients for the postoperative course, emphasising breathing exercise and sputum clearance techniques, pain control strategies and self-care. More specifically, breathing exercises focus on diaphragmatic breathing to prevent or relieve discomfort (shortness of breath, anxiety, pain), deep breathing to better ventilate all lung lobes and clearance techniques (huffing). These techniques are explained and repeatedly performed until the patient has mastered them. Self-care management involves pain relief and postural advice, as well as mobility techniques and practical advice in order to better cope with post discharge issues which could arise at home.

From day 1 after surgery until discharge patients receive daily early inpatient postoperative PR, which includes breathing exercises and positive expiratory pressure training with PEP bottle (PEP training) for a duration of 30 to 40 min every day. Upon discharge, patients are advised to continue breathing exercises and maintain an active lifestyle.

#### Intervention group

Patients allocated to the IG receive SC plus intensive PR, which includes a total of 53 sessions (14 preoperative and 39 postoperative).

##### 2.4.2.1.Preoperative intensive PR

Preoperative intensive PR is organised into six outpatient sessions performed two to three times per week, plus eight home-based sessions performed three to four times per week. The overall duration of this treatment ranges from 14 to 21 days, starting the same day the patient is listed for surgery or immediately afterwards, to minimize the delay in offering surgical treatment and to avoid the 30-day breach, as recommended by the regional guidelines [32].

Each outpatient session lasts approximately two hours and consists of an individual, supervised and personalised combination of the following elements:Therapeutic education, whose contents are the same as those provided to CG. It is delivered during the first outpatient session and repeated, if necessary, during the course of the treatment.Aerobic training, which consists of 30 to 40 min on a cycle ergometer. This training is maintained at the intensity of 60–80% peak workload (previously determined with shuttle walking test) [30] and includes a 5-min warm up and a 5-min cool down. Within this range, the intensity of training is adapted to the patient’s tolerance.Resistance training for lower limbs (extensor muscle group), upper limbs (biceps, triceps, deltoids, latissimus dorsi, pectoralis) and abdominal wall. Each exercise is performed for two to three sessions of 10 repetitions at the maximal load (previously determined with the 10-repetition maximum test) [31];RMT which includes breathing pattern training, PEP training and inspiratory muscle training for at least 15 to 30 min. Inspiratory muscle training is performed by means of a pressure threshold device, with a load ≥30% of maximal predicted inspiratory pressure; intensity is adapted to the patient’s tolerance.

Each home-based session lasts approximately one hour and consists of an individual, unsupervised and personalised combination of RMT, performed twice a day, plus 30 min of aerobic walking at the intensity of 60–80% of maximal heart rate. Patients are given a portable pedometer and a heart rate monitor and are requested to record their adherence to home-based training in the training log, which collects kilometres, steps and heart rate achieved during aerobic walking and exercises performed during RMT session.

